#### Power

Sample size estimation focused on the primary mechanistic outcomes of the study, namely preexposure to postexposure changes in EEG alpha power and performance on the 2 cognitive tasks as a function of diagnostic group (ADHD vs neurotypical) and exposure condition (real nature vs VR nature). Power calculations were conducted in G*Power (version 3.1; Heinrich Heine University Düsseldorf), using a 2 × 2 × 2 mixed-model ANOVA (group × condition × time: preexposure vs postexposure). Pilot data from a comparable ADHD sample [84] indicated a pre-to-post change in alpha amplitude of 6.93 μV (SD 2.04) at baseline and 7.88 μV (SD 1.83) postintervention, corresponding to a Cohen *d* of 0.49 (moderate effect size) for the within-subject contrast. Assuming a correlation of 0.5 among repeated measures, this maps onto a repeated-measures ANOVA effect size in the moderate range.

Using a 2-tailed α of .05 and desired power of 0.80, the required total sample size was calculated to be 64 to 72 participants (approximately 16 to 18 per cell in the 2 × 2 design) to detect effects in this range on the primary EEG outcome. To accommodate potential attrition and data loss (eg, unusable EEG recordings), a 20% buffer was applied, resulting in a final recruitment target of 80 participants (n=20 per subgroup). This sample size is expected to provide adequate statistical power to detect moderate pre-post effects and group × condition interactions on alpha power and core cognitive outcomes.

Secondary and exploratory analyses (eg, EMA trajectories, dimensional ASRS scores, and follow-up data) will be modeled using linear mixed-effects approaches in the same sample. These models are intended to characterize patterns of change over time and symptom-related gradients in responsiveness; findings from these analyses will therefore be interpreted with appropriate attention to effect sizes and precision estimates rather than relying solely on hypothesis-testing thresholds. The planned sample provides ≥80% power to detect moderate pre-post changes in alpha power for the primary group × condition × time effect in the planned linear mixed-effects analysis. Analyses of higher-order interactions and secondary outcomes (eg, EMA trajectories) will be considered exploratory and interpreted cautiously.

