#### Statistical Methods

All analyses will follow an intention-to-treat approach and will be conducted using R (R Foundation for Statistical Computing). Statistical tests will be 2-tailed with a significance level of α=.05. Descriptive statistics will summarize sample characteristics. Baseline group differences will be assessed using Pearson chi-square tests for categorical variables and independent-samples *t* tests (or nonparametric equivalents) for continuous variables. Any variables showing systematic baseline imbalance will be considered as covariates in sensitivity analyses.

To evaluate the primary outcomes—changes from preexposure (T0) to immediate postexposure (T1) in EEG alpha power, cognitive performance (Meta Mind and Star Racer), and ASRS, we will implement linear mixed-effects models (LMMs) using the *lme4* package. Fixed effects will include exposure condition (real vs VR nature), diagnostic group (ADHD vs neurotypical), time (T0 vs T1, with T9 added where relevant to examine short-term maintenance), and their interactions. Participant will be entered as a random intercept; random slopes for time will be added where supported by convergence and model fit. The primary contrasts of interest are: (1) group × condition × time for alpha power in predefined frontal and parietal regions of interest, and (2) condition × time and group × time interactions for cognitive and ASRS outcomes.

For EEG data, log-transformed alpha power (8-13 Hz) will be averaged within each region of interest and exposure phase. Within-subject change scores (T1-T0, and T9-T0 where applicable) will be analyzed in the LMM framework described above. Exploratory time-resolved effects across the 20-minute exposure will be examined using cluster-based permutation tests on epoch-wise alpha power, with family-wise error controlled at 0.05. Effect sizes will be reported as Cohen *d* for pairwise contrasts and partial eta squared (η^2^_p_) for omnibus tests.

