Secondary outcomes include trajectories of emotional well-being assessed via weekly EMA, clinical functioning in the group with ADHD (ACOS-Self), quality of life (AAQoL), and nature connectedness (NCI). EMA scores over T0-T9 will be modeled with LMMs including fixed effects for time (treated as a continuous or categorical variable depending on fit), condition, group, and their interactions, with random intercepts for participants. ACOS-Self, AAQoL, and NCI change from T0 to T9 will be analyzed using separate LMMs with fixed effects for group, condition, and their interaction. Self-reported real-world nature and VR exposure during follow-up will be explored as time-varying covariates in additional models to probe their contribution to decay or maintenance of effects.

To incorporate a dimensional perspective, *z*-scored ASRS total and subscale scores will be included as continuous predictors in a restricted set of prespecified models [85] (eg, ASRS × condition × time interactions for alpha power and cognitive outcomes). These analyses will test whether attentional trait variation predicts sensitivity to environmental exposure across the full sample, without overparameterizing models.

Multiple-comparison control will be applied at the level of outcome families: EEG (regions of interest and key contrasts), cognitive tasks (Meta Mind and Star Racer indices), EMA trajectories, and clinical measures. Within each family, *P* values will be adjusted using false discovery rate procedures; unadjusted and adjusted values will both be reported.

Model assumptions (normality of residuals, homoscedasticity, and, where relevant, sphericity) will be checked using diagnostic plots and formal tests. If assumptions are violated, transformations or robust alternatives will be considered. Missing data will primarily be handled within the mixed-model framework under a missing-at-random assumption. In addition, sensitivity analyses will be conducted using multiple imputation and complete-case subsets (participants with data at least up to T1 and T9) to examine the impact of attrition on key inferences.

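### The 80% power figure for the primary alpha-power effect is computed at unadjusted .05, but that effect is tested in at least two regions under false-discovery-rate adjustment

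*Protocol article*

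**What the plan says.** In the Power section, the calculation was made in G*Power "using a 2 × 2 × 2 mixed-model ANOVA (group × condition × time: preexposure vs postexposure"). The effect comes from a pilot "pre-to-post change in alpha amplitude of 6.93 μV (SD 2.04) at baseline and 7.88 μV (SD 1.83) postintervention", a Cohen d of 0.49. The conversion to an ANOVA effect is given only in words: "Assuming a correlation of 0.5 among repeated measures, this maps onto a repeated-measures ANOVA effect size in the moderate range". The resulting requirement is stated at one significance level: "Using a 2-tailed α of .05 and desired power of 0.80, the required total sample size was calculated to be 64 to 72 participants". For attrition and unusable recordings, "a 20% buffer was applied, resulting in a final recruitment target of 80 participants (n=20 per subgroup"). The section then claims at least 80% power for the primary three-way effect on alpha power in the planned mixed model. For the cognitive outcomes it gives no figure and calls the power only adequate. Multiplicity is not mentioned.

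In Statistical Methods, the first primary contrast is "group × condition × time for alpha power in predefined frontal and parietal regions of interest". The multiplicity paragraph reads "Multiple-comparison control will be applied at the level of outcome families: EEG (regions of interest and key contrasts), cognitive tasks (Meta Mind and Star Racer"; two further families, for EMA and clinical outcomes, are named after these. The adjustment itself is described as follows: "Within each family, *P* values will be adjusted using false discovery rate procedures; unadjusted and adjusted values will both be reported". No primary contrast is placed outside its family.

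**The concern.** The sample size answers the question of how often one test of the three-way effect gives P below .05. The plan asks a stricter question: how often that test stays below .05 after adjustment alongside the other EEG tests. An adjusted P value is never smaller than the raw one, so power under the planned rule cannot exceed the unadjusted figure, and with two or more tests it is generally lower. A primary contrast could reach .05 as the sample size was designed to allow and still fail the rule that is meant to decide it. A reader of the Power section would not know this.

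**Working it through.** **1. Inputs.** From Power: two-tailed .05, power 0.80, pilot means 6.93 and 7.88 with SDs 2.04 and 1.83, correlation 0.5, required N 64 to 72, target 80. From Statistical Methods: two alpha regions for the primary contrast, and false-discovery-rate adjustment within the EEG family. From Outcomes: three EEG indices, and six cognitive indices (three per task). Two things are assumed because the article does not state them: the procedure is Benjamini-Hochberg at 5%, and the EEG family has m = 2 tests (regions) or m = 3 (indices).

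**2. The plan's own figures.** d = (7.88 − 6.93)/√((2.04² + 1.83²)/2) = 0.95/1.938 = 0.490, which reproduces. With f = d/2 = 0.245 and the G*Power repeated-measures noncentrality λ = f² × N × 2/(1 − 0.5), the four-group within-between test (3 df) needs N = 52 and a 1-df interaction needs N = 36. Neither is 64 to 72. The 3-df test gives that range only for f of about 0.205 to 0.22, which the article does not state. The target of 80 equals 64/0.8; 72/0.8 would be 90. So the unadjusted power at the evaluable N cannot be fixed from the text, and two cases are needed.

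**3. Case A: unadjusted power is exactly 80% at the evaluable N.** The noncentrality on the z scale is 1.960 + 0.842 = 2.802.
- *m = 2.* The threshold for the smaller P value is .025 (z = 2.241), with power Φ(2.802 − 2.241) = 0.712. The test also passes if its P value lies between .025 and .05 and the other test is below .05. For independent tests:
  - only this region real: 0.712 + (0.80 − 0.712) × 0.05 = 0.716, about 72%;
  - both regions real: 0.712 + (0.80 − 0.712) × 0.80 = 0.782, about 78%.
- *m = 3.* At .05/3 (z = 2.394) power is Φ(2.802 − 2.394) = 0.658. Simulation of the full procedure, with independent tests and with correlation 0.5, gives about 66% if one effect is real and 76% to 78% if all three are. For m = 2 the simulation gives 72%, and 77.5% to 78%.

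**4. Case B: the pilot effect taken literally.** With f = 0.245, r = 0.5, 64 evaluable and the 3-df test, λ = 0.245² × 64 × 4 = 15.37. The worst-case threshold, when only one effect in the family is real, is .05/m.

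| Threshold | Power |
|---|---|
| .05 (unadjusted) | 90.5% |
| .025 (m = 2) | 84.4% |
| .0167 (m = 3) | 80.2% |

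The 1-df version gives 97%, 94% and 92%.

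**5. Cognitive outcomes.** The same adjustment applies to at least six indices. No power figure is stated for them, so there is no stated number to set a loss against.

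**The case against.** The strongest reply is that 80% may well survive. Case B shows this for two or three EEG tests if the pilot effect is accepted as the protocol uses it. That stands, and it limits the point. A reader might infer that power must fall below 80% even when the assumed effect is right, or that 72% to 78% is the true power. The documents support neither, because both need unadjusted power of exactly 80%, which the stated inputs do not yield.

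A reader might also multiply six cognitive indices by two contrasts and report a very large shortfall. The article claims 80% only for alpha power and does not count contrasts in the cognitive family, so that would not be a shortfall from a stated figure.

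The Introduction expects distinct prefrontal and parietal change, so both regions may respond. The Case A loss is then only about 2 points. That is fair, but distinct patterns do not amount to equal three-way interactions in both regions.

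The 20% buffer helps only if little data is lost. With all 80 evaluable, an effect with 80% power at N = 64 keeps about 81% at .025 and 77% at .0167. One with 80% power at N = 72 has about 76% at .025.

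It could be said that reporting both P values leaves the deciding one open. If the unadjusted value decided, the stated multiplicity control would have no effect.

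Lastly, using a within-subject pre-post d for a three-way interaction is a separate problem. Repairing it would not remove this one, since a new calculation at unadjusted .05 would repeat the mismatch.

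**Conclusion.** The point holds as a mismatch between two things the article itself fixes: power at a single unadjusted .05, and a primary alpha-power effect judged in at least two regions after false-discovery-rate adjustment. The stated figure of at least 80% is not the power of the planned test. The loss is about 2 to 8 points for two regions and about 2 to 14 points for three indices if unadjusted power is exactly 80%. If unadjusted power is about 90%, the claim of 80% can survive both family sizes. These ranges rest on Benjamini-Hochberg at 5%, family sizes read from the listed regions and indices, and correlation between tests of 0 to 0.5. The mismatch is worth correcting before enrolment, but it does not show that the trial is underpowered.

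**What to change.** In the Power section, recompute and restate the alpha-power figure under the adjusted rule in Statistical Methods. State the effect size for the contrast actually tested, the number of tests in the EEG family and the assumed number of real effects. Do this in the same recalculation as any correction of the effect-size basis. Do not insert 72% to 78% as the replacement figure, since it depends on an unadjusted power that the inputs do not establish. Qualify the statement that cognitive power is adequate in the same way, for at least six adjusted indices.

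The cost is a short recalculation and a few sentences. The stated power may look less favourable. The restatement itself needs no extra participants.

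### The required total of 64 to 72 does not follow from the effect size, correlation, design, alpha and power stated for it

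*Protocol article*

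**What the plan says.** All of this is in the protocol article, Statistical Analysis, Power.

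- Design and software: G*Power 3.1, "using a 2 × 2 × 2 mixed-model ANOVA (group × condition × time: preexposure vs postexposure"). That means four between-subject cells and two measurements.
- Pilot data: alpha amplitude of "6.93 μV (SD 2.04) at baseline and 7.88 μV (SD 1.83) postintervention". The article expresses this pre-post difference as d = 0.49 and calls it moderate.
- Conversion: "Assuming a correlation of 0.5 among repeated measures, this maps onto a repeated-measures ANOVA effect size in the moderate range". No value of f is printed.
- Error rates: "Using a 2-tailed α of .05 and desired power of 0.80".
- Result: the article reports that "the required total sample size was calculated to be 64 to 72 participants", which it equates with some 16 to 18 in each of the four cells.
- Buffer: 20% for attrition and unusable EEG, giving 80 (20 per cell).

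The section closes by claiming at least 80% power in connection with the group × condition × time effect. Under Statistical Methods, that three-way term is the first primary contrast for alpha power.

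**The concern.** The section prints its inputs and its output, so the output can be checked. An effect of this size, with two measurements correlated at 0.5, usually needs far fewer than 64 participants in a repeated-measures ANOVA. If 64 to 72 does not follow, the power of 0.80 attached to it is not the power of the calculation described.

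This matters because 64 to 72 is the only stated basis for the target of 80, for the loss allowance and for the closing power claim. A reader also cannot tell which term was powered, although the primary alpha contrast is one particular interaction.

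**Working it through.** **Inputs from the Power section.** Means 6.93 and 7.88, SDs 2.04 and 1.83, d = 0.49, r = 0.5, m = 2 measurements, k = 4 cells, alpha .05, power 0.80.

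**Step 1: the stated d is right.** The difference is 7.88 − 6.93 = 0.95. The pooled SD is √((2.04² + 1.83²)/2) = √3.755 = 1.938. So d = 0.95/1.938 = 0.490. The standardised mean change at r = 0.5 is almost the same: 0.95/√(2.04² + 1.83² − 2·0.5·2.04·1.83) = 0.489.

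**Step 2: convert to f.** For two measurements, f = d/2 = 0.245. This is an inference, because the article says only that the effect is moderate. The conventional medium value, f = 0.25, is carried alongside.

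**Step 3: required N with the default repeated-measures option.** The test is a noncentral F with λ = f²·N·m/(1 − r) and denominator df = N − 4, with N rounded up to equal cells. Here λ = 0.060025 × N × 2/0.5 = 0.2401·N.

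| Term tested | N at f = 0.245 | λ | Power at that N | N at f = 0.25 |
|---|---|---|---|---|
| 1 df (time effect, or one interaction assumed to have this f) | 36 | 8.64 | 0.813 | 36 |
| 3 df (cell × time) | 52 | 12.49 | 0.823 | 48 |

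Neither row reaches 64. Reading the effect as the conventional medium value does not raise N.

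**Step 4: power at the stated N, same formula.**

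| N | λ | 1 df | 3 df |
|---|---|---|---|
| 64 | 15.37 | 0.971 | 0.905 |
| 72 | 17.29 | 0.984 | 0.939 |
| 80 | 19.21 | 0.991 | 0.961 |

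**Step 5: other routines at f = 0.245.** These also miss the range:

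- between-subject test: 102 (two groups), 104 (four cells, 1 df) or 144 (four cells, 3 df);
- SPSS-type effect-size option: 140 or 192;
- Cohen-type option: 134, 136 or 188.

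**Step 6: what does give 64 to 72.** Each route departs from the calculation as described.

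- A smaller effect: 3 df, r = 0.5, f from 0.213 (N = 64) down to 0.200 (N = 72).
- A lower correlation at f = 0.245: r from 0.34 to 0.25 with 3 df, or from about 0.05 to −0.07 with 1 df.
- Power 0.90 with 3 df: N = 64.
- A stricter alpha with 3 df: .0167 gives 64 and .01 gives 72.
- A paired pre-post test powered separately in each diagnostic group: 35 × 2 = 70 (exact t) or 33 × 2 = 66 (normal approximation).
- An incomplete conversion: f = 0.245/√(1 − 0.5) = 0.346, entered under the Cohen-type or SPSS-type option with 1 df, gives 68 or 72. This drops the factor for two measurements. The full conversion is 0.245·√(2/0.5) = 0.49, which gives 36 or 40.

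**Step 7: the buffer.** Dividing by 1 − 0.20 gives 64/0.8 = 80 and 72/0.8 = 90. Starting from 80, falling to 64 is a loss of 16/80 = 20%, and falling to 72 is a loss of 8/80 = 10%.

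**The case against.** The strongest reply is that the section does not state everything the software needs. It gives no f, tested term, numerator df or effect-size option, and it speaks of effects in a range, which could explain a range of N. An article may leave such settings to the full protocol, and the study was preregistered with its planned analyses. The discrepancy is also on the safe side and changes no recruitment decision.

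Much of this stands. The missing settings are not themselves the fault, and f = 0.245 is inferred. But the printed inputs and output disagree under either choice of df, and f = 0.25 moves N further from 64. The effect that would give 64 to 72 on the 3-df term is about 0.20 to 0.21, below both the stated effect and the conventional medium value.

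Two stronger readings are tempting, and the document does not support them.

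- A reader might infer that the stated correlation or effect size must have been swapped for another. Several routes in step 6 keep d = 0.49 and r = 0.5, so the source of the figure cannot be identified. What is shown is that the calculation as described does not give it.
- A reader might infer that 36 or 52 would suffice, or that the trial is overpowered for its main question. Those figures carry a pre-post effect, and the 3-df term pools group × time, condition × time and the three-way term. The primary alpha contrast is the three-way difference in change, and no effect size is given for it. As an illustration only, assume a three-way contrast of D SDs of change. With N/4 per cell, λ = D²·N/16. D = 0.49 then needs about 528, with power of 0.16 to 0.19 at N = 64 to 80; D = 0.98 needs about 136.

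**Conclusion.** The point holds as a failure to reproduce. Under the stated design, d, r, alpha and power, and with f taken as d/2 and the default effect-size option, the required N is 36 (1 df) or 52 (3 df). The stated 64 to 72 exceeds these by 28 to 36 or by 12 to 20. The stated power of 0.80 would be 0.97 to 0.98 or 0.90 to 0.94 at that N.

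Relative to its own inputs the error is conservative, so it does not count against recruiting 80. The 20% allowance is met only at the lower end of the range. None of this shows adequate power for group × condition × time: the power claim attached to that term rests on a pre-post effect and is unsupported as written.

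**What to change.** Re-run the calculation and replace the 64 to 72 statement with one that follows from its inputs. State f and how it was obtained from d, the term tested, its numerator df, r, the effect-size option, and why the result is a range if one is kept. If 64 to 72 is retained, print the inputs or the test that produce it.

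Keep the target of 80. State the power at 80 for the term actually calculated, and the loss allowance that 80 supports (20% down to 64, 10% down to 72). If 36 or 52 is reported, label it as applying to a pre-post effect, or to a term assumed to have f = 0.245, and not as the N required for the three-way contrast. Remove the claim of at least 80% power from that contrast unless an effect size for it is stated and used.

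The cost is one re-run and a few sentences in the Power section, with no change to recruitment.

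### The ≥80% power claimed for the group × condition × time effect on alpha rests on a single-sample pre-post effect; a three-way difference of that size would have about 16–19% power

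*Protocol article*

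**What the plan says.** The Power section of the protocol article takes its effect size from a pilot ADHD sample: alpha amplitude 6.93 μV (SD 2.04) before and 7.88 μV (SD 1.83) after an intervention. It reports this as a Cohen d "of 0.49 (moderate effect size) for the within-subject contrast", assumes a correlation of 0.5 between repeated measures, and says that this corresponds to a moderate repeated-measures ANOVA effect. It does not give the f that was entered or the model term that was tested.

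With a "desired power of 0.80, the required total sample size was calculated to be 64 to 72 participants", which comes to 16 to 18 in each of the four cells. To allow for losses, "a 20% buffer was applied, resulting in a final recruitment target of 80 participants". The section calls this sample adequate for moderate pre-post effects and for group × condition interactions on alpha power and the core cognitive outcomes. It then states: "The planned sample provides ≥80% power to detect moderate pre-post changes in alpha power for the primary group × condition × time effect". The next sentence reads: "Analyses of higher-order interactions and secondary outcomes (eg, EMA trajectories) will be considered exploratory and interpreted cautiously".

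The Statistical Methods section gives the three-way term primary status: "The primary contrasts of interest are: (1) group × condition × time for alpha power in predefined frontal and parietal regions of interest".

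**The concern.** A one-sample pre-post change shows how much alpha moves on average after an exposure. It does not show whether real and VR nature move it by different amounts, still less whether that difference depends on ADHD status. The three-way term is a difference of differences of changes. With equal cells its standard error is four times that of the pooled change, so an effect size taken from the pooled change cannot carry the same power across.

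At stake is how a non-significant result would be read. With 80% power on record, readers would take a null three-way test as evidence that ADHD does not alter the real-versus-VR response, which bears on the second core question in the Introduction. If the interaction is no larger than the pilot change itself, a null result is by far the likelier outcome even though the difference is real.

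**Working it through.** **Inputs.** From Power: means 6.93 and 7.88 μV, SDs 2.04 and 1.83, r = 0.5, evaluable N of 64 to 72, recruited N of 80 in four equal cells. From Statistical Methods: "Statistical tests will be 2-tailed with a significance level of α=.05".

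**1. Reproduce d.** The change is 7.88 − 6.93 = 0.95 μV. The pooled SD is √[(2.04² + 1.83²)/2] = 1.938, so d = 0.95/1.938 = 0.490. The SD of change at r = 0.5 is √(2.04² + 1.83² − 2 × 0.5 × 2.04 × 1.83) = 1.944, so the standardised change is 0.95/1.944 = 0.489. The stated 0.49 reproduces.

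**2. Try to reproduce N = 64 to 72.**
- A paired pre-post test at 0.49 needs 35 people for 80% power.
- With f = d/2 = 0.245 and λ = f² × N × 2/(1 − r), a 1-df test needs N = 36. The 3-df test of time across four cells needs N = 52.
- On that 3-df omnibus test, 64 to 72 corresponds to f of about 0.22 down to 0.205. The omnibus test is not the three-way term.
- Two conditions of 35 each make 70, inside the range and consistent with a pre-post calculation, but the article does not say this was done.

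**3. Power by contrast at 0.49 SD of change.** In SD-of-change units, with N/4 per cell:
- pooled pre-post change: SE = √(1/N), 0.125 at N = 64
- two-way interaction with time: SE = √(4/N), 0.25 at N = 64
- three-way: SE = √(16/N), 0.50 at N = 64

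The noncentrality is 0.49/SE (3.92, 1.96 and 0.98 at N = 64) and df = N − 4.

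| Contrast | N = 64 | N = 72 | N = 80 |
|---|---|---|---|
| Pooled pre-post change | 97% | 98% | 99% |
| Two-way interaction with time | 49% | 54% | 58% |
| Three-way | 16% | 18% | 19% |

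Simulation of the three-way test (20,000 runs per setting) gave 16.5%, 17.4% and 19.0%. About 528 evaluable participants would be needed for 80% power.

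**4. Range over the correlation.** These correlations other than 0.5 are assumptions; 0.95 μV is kept and N runs from 64 to 80.

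| r | SD of change (μV) | Standardised change | Three-way power |
|---|---|---|---|
| 0.3 | 2.296 | 0.414 | 13–15% |
| 0.5 | 1.944 | 0.489 | 16–19% |
| 0.7 | 1.511 | 0.629 | 24–28% |
| 0.8 | 1.240 | 0.766 | 33–39% |

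**5. Range over the size of the three-way difference** (r = 0.5, N = 64 to 80). Half of 0.49 SD gives about 8%; twice (0.98 SD) gives 49–58%; four times (1.96 SD) gives 97–99%. The difference detectable with 80% power is 1.42 SD (2.8 μV) at N = 64, 1.34 SD (2.6 μV) at N = 72 and 1.27 SD (2.5 μV) at N = 80.

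**6. The reading under which 80% is reached.** Suppose 0.245 is the f of the interaction itself. At r = 0.5, λ = 4f²N. For a three-way difference Δ in SD of change, the squared noncentrality is Δ²N/16. Equating the two gives Δ = 8f = 1.96 SD, or 1.96 × 1.944 ≈ 3.8 μV, four times the pilot change.

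**The case against.** The strongest defence is the reading in step 6. The article does not say how d was converted. If about 0.245 was entered as the interaction's own f, a 1-df test passes 80% power at N = 36, so the claim is arithmetically true at 64 to 80. The calculation would then be sound, but its effect size would have no basis. Without lower-order interactions, a difference of 1.96 SD puts the cells at +0.49 and −0.49 SD around the common change: a full crossover, with VR ahead of real nature in one diagnostic group. The Introduction expects both exposures to produce restorative EEG change, more strongly for real nature. This reading also yields 36 or 52 participants, not 64 to 72.

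Other points limit what can be concluded:

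- A reader might take 16–19% as the true power. It is conditional on a three-way difference equal to the pilot change and on r = 0.5; the article states no size for that difference.
- A reader might infer that the test will be null whatever the truth. Power is 49–58% at 0.98 SD and 80% at 1.27 to 1.42 SD, so this does not follow.
- The sentence calling higher-order interactions exploratory might look like a flat contradiction. It may mean terms beyond the named primary one, such as the ASRS × condition × time models. It is ambiguous.
- The 20% buffer might look miscalculated. It is not: 80 × 0.8 = 64, which lies within the stated 64 to 72.
- The absence of condition × time from the primary alpha contrasts might look like an error. It is a design choice: the term is in the model, and it is a primary contrast for cognition. At 0.49 SD and r = 0.5 it would itself have only 49–58% power.
- The Discussion concedes that sample size may constrain interaction estimates. That sentence concerns dimensional modelling and does not withdraw the 80% claim.

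**Conclusion.** The power statement is wrong as written. Its only effect size belongs to the time effect, for which the sample is ample (97–99%), and it is attached to a three-way contrast for which no effect is stated. On the plan's own inputs, a three-way difference as large as the whole pilot change has 16–19% power at N = 64 to 80, and 13–39% over correlations from 0.3 to 0.8. A smaller interaction has less. The statement that the sample is adequate for group × condition interactions fails for the same reason: on change scores, that term for alpha is the three-way contrast.

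The figures assume equal cells and analysis of change. They precede the false discovery rate adjustment within the EEG family, which cannot raise power. The pilot is in amplitude (μV) while the analysis uses log-transformed power, so the mapping is approximate. None of this shows that the three-way test is bound to fail or that the choice of primary contrast is mistaken; it shows that the stated power for it is unsupported.

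**What to change.** In the Power section:

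- Limit the 80% statement to the pooled pre-post change in alpha.
- Withdraw it for the three-way effect, and withdraw the adequacy statement for group × condition interactions. The alternative is to state and justify a three-way difference with its SD and recompute.
- Give the three-way difference detectable with 80% power: 1.42 SD of change at 64 evaluable participants, 1.34 at 72 and 1.27 at 80, at r = 0.5 and before multiplicity adjustment.

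In the Power and Statistical Methods sections together, say whether the three-way term is primary or belongs with the exploratory higher-order interactions. Commit to reporting its estimate with a confidence interval, and to not reading a non-significant result as evidence that ADHD makes no difference.

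The cost is wording in two sections and matching updates to the registrations. Recruitment had not begun at submission, and no more participants are needed. The price is a less favourable power statement.
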